## Abstract

**Introduction:**

Falls are a significant concern for older adults, particularly those with neurological, vestibular, cognitive and post-viral conditions, due to dizziness and imbalance. Conventional balance rehabilitation programmes, though effective, face challenges in adherence and accessibility. The TeleRehabilitation Decision Support System (TeleRehaB DSS) uses artificial intelligence (AI) and motion tracking to provide individualised multisensory balance rehabilitation (MBR) remotely. This trial aims to evaluate the acceptability, feasibility, safety and preliminary efficacy of a home-based TeleRehaB DSS among community-dwelling older adults at risk of falls due to stroke, mild cognitive impairment (MCI), long COVID and vestibular dysfunction.

**Methods and analysis:**

This multicentre, assessor-blinded randomised controlled trial will recruit 460 community-dwelling adults aged 40–80 years with stroke, MCI, vestibular dysfunction or long covid across five sites in the UK, Europe and Southeast Asia. Participants will be randomised to a 9-week remotely supervised home exercise programme using either TeleRehaB DSS (high-tech or low-tech MBR with exergames and cognitive training) or standard care (OTAGO home exercise programme or Meniere’s Dizziness booklet). Primary outcomes include feasibility, acceptability and safety, alongside clinical measures of balance and health-related quality of life (Functional Gait Assessment, EuroQol five-dimensional descriptive system instrument). Secondary outcomes assess balance, cognition, physical activity, dizziness, psychological well-being, fatigue and confidence. Usability, user experience and digital health literacy will also be evaluated. Anonymised data will undergo quality checks and be analysed using descriptive and exploratory statistics, mixed-effects models, cost-effectiveness analysis (incremental cost-effectiveness ratio) and thematic analysis of qualitative interviews, adjusting for site and relevant confounders.

**Ethics and dissemination:**

This study has received institutional ethical approvals in the UK, Germany, Greece and Thailand and from Madeira, Portugal. Findings from this study will be submitted for peer-reviewed publications.

**Trial registration number:**

NCT06534164.

STRENGTHS AND LIMITATIONS OF THIS STUDYThis multicentre, assessor-blinded randomised controlled design strengthens internal validity while assessing the feasibility and acceptability of the TeleRehabilitation Decision Support System (TeleRehaB DSS) intervention compared with a standard home exercise programme.The mixed-methods approach enables triangulation of quantitative usage metrics with qualitative user experiences to comprehensively assess acceptability and usability.The multicentre recruitment across several international sites may introduce variability in implementation and participant support despite use of a standardised protocol.As a feasibility study, the sample size is not powered to detect clinical effectiveness outcomes.Reliance on participant self-setup and home use of technology may influence adherence and data completeness.

## Introduction

### Falls epidemic

 Falls are a rising epidemic among older adults, occurring annually in 30% of adults aged over 65 years, with wide-ranging physical, psychosocial and healthcare-related consequences.^1 2^ The Global Burden of Diseases study reported nearly 17 million years of life lost from falls in 2017, with the expected number of falls and related injuries likely to further increase with the ageing population.^3^,^5^

Falls are multifactorial, especially during performance of complex tasks, when falls are most likely to occur.^6^ Impaired balance and dizziness have consistently been identified as risk factors for falls which are associated with multiple comorbidities, including stroke, mild cognitive impairment (MCI), vestibular dysfunction and long COVID.^7^,^10^ Balance and mobility problems are among the most frequent and disabling effects of stroke, with two-thirds of survivors experiencing residual degrees of disability^11^,^13^ with falls as one of the most commonly resulting consequences.^14 15^ Although less studied in middle-aged adults compared with older adults, falls are a significant issue among both groups,^16^ with studies indicating that fall rates remain high in middle-aged adults post-stroke, particularly among those with residual functional limitations.

Compromised cognitive function, as in individuals with MCI and/or long COVID, is also associated with increased risk of falls due to reduced executive function and attention and slow processing speeds which affect balance and gait.^7 17 18^ Adults with MCI have a notably higher incidence of falls compared with those with normal cognitive function.^7 18^ Similarly, emerging evidence has found that the long-term effects of COVID-19, known as long COVID, can include persistent symptoms of cognitive decline, fatigue, muscle weakness and balance issues, all contributing to an increased risk of falls.^10 19 20^ Furthermore, vestibular disorders, including central (stroke, multiple sclerosis, cerebellar disease) and peripheral (i.e., unilateral vestibular hypofunction, vestibular neuritis, labyrinthitis) causes, directly impair balance and spatial orientation, significantly increasing the likelihood of falls.^9 21 22^

### Balance rehabilitation

Balance is complex, relying on integration of vestibular, visual and somatosensory inputs for postural orientation and motion while central processes monitor and control the interaction between musculoskeletal and neural systems to generate anticipatory postural adjustments and adapt posture to changing environmental and balance task demands.^1423^,^25^ Previous studies have indicated that multisensory balance rehabilitation (MBR) can improve dynamic balance.^23^,^27^ MBR consists of exercises that aim to improve balance, gait, somatosensory integration and gaze stability through compensation, adaptation, habituation and/or substitution of the vestibular ocular reflex and/or vestibulospinal reflex.^28^,^30^ Multisensory exercises, consisting of activities simultaneously stimulating at least two sensory modalities, including visual, auditory, tactile, vestibular and somatosensory systems, are effective for improving balance in people with balance disorders.^24^ MBR programmes which address balance have shown substantial reduction in falls risk in older adults, compared with standard programmes.^231^,^33^

Balance rehabilitation is the most effective treatment for balance disorders across all ages, typically involving personalised exercises prescribed by healthcare professionals.^21 34 35^ However, access to specialist services is often limited due to resource and staffing constraints. While effective in reducing fall risks among older adults, balance/falls programmes face challenges such as poor adherence, with up to 50% of participants dropping out early.^3436^,^38^ Common limitations include inadequate exercise progression, lack of individualisation and minimal supervision, and they often fail to address real-world situations such as dual-task training or activities simulating everyday challenges (eg, crossing a road).^1734 36^,^38^

Studies concerning the effect of MBR on balance and gait outcomes among stroke survivors, MCI, vestibular dysfunction and long covid are limited,^27^ and even in persons with vestibular dysfunction where multiple studies exist, optimal treatment strategies are still unknown.^9 21 39 40^ Balance rehabilitation programmes are rarely multisensory and commonly lacking a cognitive element, which are key factors in addressing static and dynamic balance.^17 41 42^ Further research is needed to investigate the optimal MBR for these populations.^43^

### Digital health technologies

Recent advancements in digital health technologies have enabled innovative approaches to rehabilitation delivery, including remote and home-based interventions.^44^ Telerehabilitation, the remote provision of rehabilitation by means of information and communication technologies (ICT), provides a promising solution to address these challenges. Emerging evidence suggests that ICT, such as wearable sensors, computerised decision support systems, extended reality (augmented or virtual reality) and telerehabilitation platforms, have the potential to improve clinical efficiency and satisfaction and enhance care quality, while reducing healthcare costs.^45^ Compared with traditional in-person training, telerehabilitation has been shown to improve patient accessibility while overcoming socioeconomic, geographical and cultural challenges.^43 46 47^ Furthermore, data from the HOLOBalance project have shown improved balance and gait outcomes in non-neurological fallers, following remotely delivered MBR via augmented reality (AR).^47^

The TeleRehabilitation Decision Support System (TeleRehaB DSS), evolved from its predecessor, HOLOBalance,^48^ leverages artificial intelligence (AI) and motion tracking with real-time feedback to offer remotely delivered individualised MBR via AR, addressing the lack of expert balance physiotherapists. Delivered in the comfort of patient’s home, it offers an interactive rehabilitation programme incorporating (1) functional training, (2) multisensory balance exercises, (3) cognitive training and (4) gamified activities (exergames).

### Aims

TeleRehaB DSS will use off-the-shelf technologies to enable remotely monitored MBR for adults at risk of falls due to either stroke, MCI, vestibular dysfunction or long covid. This study protocol outlines the global, multisite randomised controlled trial (RCT) that aims to (1) determine the system’s safety, acceptability and feasibility; (2) assess how quality of life (QOL), balance function and confidence, cognitive function and well-being compare to standard of care interventions following a 9-week balance programme; and (3) provide preliminary data for a definitive randomised controlled trial.

## Methods

### Trial design

The study is a multicentre, assessor-blinded RCT, investigating the feasibility and acceptability of the TeleRehaB DSS in persons with stroke, MCI, vestibular dysfunction or long covid.^49^ All participants will be enrolled in a 9-week MBR home exercise programme (HEP), including individualised balance exercises (sitting, standing, walking), cognitive training and exergames (figure 1). All participants will be randomised into one of three study arms, where they will receive a HEP provided under the supervision of a clinician (physiotherapist or sports scientist): (1) the high-technology TeleRehaB DSS group (HT-IG), (2) the low-technology TeleRehaB DSS group (LT-IG) or (3) the control group (CG) standard of care HEP. No matter the study arm allocated, all participants will receive the same prescription pattern, receiving a weekly check-in call by a member of the research team, and remote programme reviews at weeks 3 and 6 by the treating clinician, to discuss exercise modifications, symptoms, falls and any technical problems.

**Figure 1 F1:**
[figure not shown]
Screenshots of (**A**) physiotherapist avatar and (**B**) representative exergame from the TeleRehab DSS. TeleRehab DSS, TeleRehabilitation Decision Support System.

Exercise data will be collected automatically in TeleRehaB DSS dashboard for the HT-IG and LT-IG, whereas CG participants will be required to log their exercise data manually in a diary provided. Exercises will be prescribed and progressed according to participant feedback and task performance, as assessed by the treating clinician. All treating clinicians will receive appropriate training prior to trial onset.

This study will compare acceptability of the TeleRehaB DSS programme (adherence, recruitment and dropouts) compared with current standard of care (OTAGO or Balance Retraining Booklet), which are commonly used in balance and vestibular rehabilitation. This study will also explore trends for effectiveness across several validated clinical outcome measures to identify whether a future trial is warranted and if so, to provide sample size estimates. The protocol has been developed using the Standard Protocol Items: Recommendations for Interventional Trials reporting guidelines^50^ and the flow of participants through the trial will be recorded in compliance with the Consolidated Standards of Reporting Trials statement^51^ (figure 2).

**Figure 2 F2:**
[figure not shown]
CONSORT diagram to demonstrate participant flow through the TeleRehaB DSS RCT. After baseline testing and randomisation, participants were allocated to either the intervention group, comprising a high-technology arm and low-technology arm, or the control group. The control group consisted of participants receiving either the OTAGO HEP or a vestibular-specific HEP. Assessments were conducted at baseline, week 3 (review 1), week 6 (review 2) and week 10 (final assessment). Participant numbers, dropouts and reasons for loss to follow-up or intervention discontinuation were recorded at each stage. Final analysis was performed according to group allocation, noting any exclusions. CONSORT, Consolidated Standards of Reporting Trials; HEP, home exercise programme; RCT, randomised controlled trial; TeleRehaB DSS, TeleRehabilitation Decision Support System.

### Study setting

The study will take place across five clinical sites (London, UK; Freiburg, Germany; Athens, Greece; Madeira, Portugal; and Bangkok, Thailand).

### Participants

Independently living, community-dwelling older adults aged 40–80 years who are at risk of falls, and clinically diagnosed with either stroke, MCI, vestibular dysfunction or long covid, will be recruited across the five clinical sites.

#### Inclusion criteria

All participants must meet the below criteria for consideration in the study, with additional specific criteria for each disease cohort (table 1).

**Table 1 T1:** TeleRehaB DSS clinical study inclusion criteria

All participants	Age 40–80 years. Community dwelling able to walk 500 m independently or with a stick. HADS depression subscale score <10/21. No significant visual impairment (as self-reported by participants). Willing to comply with study procedures, proposed training and testing regime. Able to understand and consent to the research. Has at least one functional hand for grip function and computer use. Fulfilling all of the criteria from one of the below subgroups
Stroke participants	Individuals with diagnosis of focal ischaemic or haemorrhagic stroke, as confirmed by a clinical letter. Onset >6 months prior to study. MoCA score >23. FGA score <22/30 AND/OR having experienced a fall(s) in the last 12 months. If diagnosed with drop foot, must have a corrective device (AFO, FES etc.) must be in-place for exercise performance.
MCI participants	Individuals with diagnosis of MCI, according to the ICD10 (G31.84),^92^ as confirmed by a clinical letter. FGA <22/30 AND/OR having experienced a fall(s) in the last 12 months.
Vestibular dysfunction participants	Individuals with a diagnosis of a vestibular disorder (peripheral and/or mixed peripheral and central) as confirmed by a clinical letter: Peripheral vestibular disorder in which the balance problem lies in the vestibular/balance system within the inner ear. Mixed vestibular disorder in which the balance problem lies in the vestibular/balance system within the inner ear (peripheral) and involving the nerves or neuronal network in the brain/brainstem responsible for balance (central). Chronic dizziness and/or unsteadiness (>3 months duration) due to a vestibular disorder. DHI score >34 AND/OR FGA score <22/30. MoCA score >23.
Long covid participants	Individuals with laboratory confirmed diagnosis of COVID-19 (>6 months prior to study onset) AND/OR who have been diagnosed with long covid, as confirmed by a clinical letter. Who have chronic dizziness and/or unsteadiness which started after the COVID-19 illness (self-report by the patient; duration >3 months). DHI score >34 AND/OR FGA score <22/30. MoCA score >23.

AFO, ankle-foot orthoses; DHI, Dizziness Handicap Inventory; FES, Functional Electrical Stimulation; FGA, Functional Gait Assessment; HADS, Hospital Anxiety and Depression Scale; ICD10, International Classification of Disease 10; MCI, mild cognitive impairment; MoCA, Montreal Cognitive Assessment; TeleRehaB DSS, TeleRehabilitation Decision Support System.

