#### Sample size

The target sample size across all sites is 460. This equates to 60–100 participants per clinical site, with 30–50 participants recruited to intervention group (IG) and CG study arms, per clinical site, in line with recommendations for pilot feasibility studies.^49 52 53^

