#### Recruitment

Each clinical site will recruit participants via (1) web-based advertisements, (2) social network groups, (3) relevant local patient bodies (for stroke, MCI, balance/dizziness problems, long covid), (4) specialist consultants and/or (5) research staff. Potential participants will undergo a telephone screening session with a researcher to determine their eligibility, with eligible participants booked in for baseline testing with the blinded outcome assessor. Participants will provide written informed consent (online supplemental appendix 1) upon arrival at their baseline outcome assessment session.

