#### Randomisation and blinding

Participants’ will be randomised using an online platform (www.sealedenvelope.com), and opaque envelopes, into either the HT-IG, LT-IG or CG to undergo a HEP. Participants will not be able to choose their preferred group and must be willing to participate in the assigned group. Details of the randomisation procedure, eligibility screening and intervention procedure can be found in figure 3.

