#### Primary outcome measures

Primary outcomes of feasibility, acceptability, usability and safety will be investigated alongside clinical measures of Functional Gait Assessment (FGA) and EuroQol five-dimensional descriptive system (EQ-5D-5L) instrument pre-intervention and post-intervention. The FGA includes 10 tasks that assess dynamic and complex gait (eg, walking with head turns or stopping and turning), with a minimal detectable change (MDC) of 4.2 points in stroke populations and 6 points in vestibular disorders^61^ and minimally clinically important difference (MCID) of 4 points in community-dwelling older adults.^62 63^

Programme effectiveness will be evaluated using quality-adjusted life years (QALYs) measured with the EQ-5D-5L instrument.^64^ The EQ-5D-5L is a standardised, valid and reliable measure of health status for clinical and economic appraisal.^64^ The respondent is asked to rate their health status on five dimensions (mobility, self-care, usual activities, pain/discomfort, anxiety/depression), followed by a self-rated health score from 0 to 100. MCID ranges from 0.03 to 0.52.^65^,^67^

Primary outcomes are as follows:

*Acceptability*: recruitment (percentage of eligible participants enrolled); dropout rates; intervention adherence (percentage of prescribed sessions completed) monitored automatically through the system for TeleRehaB DSS participants and via an exercise diary for control groups.*Safety*: participants will be monitored for adverse event’s via completion of adverse events forms on the system database, during telephone or face-to-face contacts as part of the intervention phase and during follow-up assessments. Falls diaries will be collected weekly from participants during the intervention, and monthly for up to 6 months after completion of the intervention.*Feasibility*: protocol deviation (PD) or study protocol implementation problems (eg, logistical).*Usability*: participants’ experience using the system (perceived benefits, frustrations and recommendations) will be explored via exit interviews for all TeleRehaB DSS group completers. These participants will also complete the SUS^68^ and UEQ^69^ to explore system usability and user experience, respectively.

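### Willingness to follow the regime is an eligibility criterion, so the primary recruitment rate cannot register people who decline it at telephone screening

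*Protocol article*

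**What the plan says.** Four statements in the protocol article bear on the point.

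- Inclusion criteria: "All participants must meet the below criteria for consideration in the study". The list for all participants in Table 1 includes "Willing to comply with study procedures, proposed training and testing regime".
- Recruitment: "Potential participants will undergo a telephone screening session with a researcher to determine their eligibility". Those found eligible are booked for baseline testing, and written consent follows "upon arrival at their baseline outcome assessment session".
- Primary outcome measures: acceptability is measured by dropout, adherence and "recruitment (percentage of eligible participants enrolled". The Trial design section (text after Figure 1) names the same three components: "This study will compare acceptability of the TeleRehaB DSS programme (adherence, recruitment and dropouts").
- Randomisation and blinding: "Participants will not be able to choose their preferred group and must be willing to participate in the assigned group". This sentence is not part of Table 1.

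The article sets no expected or minimum recruitment rate.

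**The concern.** Recruitment is one of three primary measures of acceptability. For it to say anything about acceptability, a suitable person who turns the programme down has to count against it. Here willingness is one of the conditions for being eligible, and eligible people form the denominator. A person who meets the clinical criteria but tells the screener that they do not want the training is then recorded as ineligible, not as a refusal.

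Dropout and adherence cannot make up for this, since both start after enrolment. Of the three acceptability measures, recruitment is the only one that could pick up refusal at first contact. A reader of the final report would take the percentage as uptake among suitable patients, and it would be higher than that. If some of the five sites log decliners as eligible and others as ineligible, the pooled figure would also mix two definitions.

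**Working it through.** The article states no recruitment rate, so there is no figure to reproduce. The check has three steps.

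**1. Where each person is counted under the stated rules**

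- Declines the training or testing at the telephone call: fails a Table 1 criterion, so is in neither numerator nor denominator.
- Passes the call, then does not attend or does not consent: eligible and not enrolled, so in the denominator.
- Declines because of random allocation: unclear. The requirement stands under Randomisation and blinding as a condition of taking part, and the article does not say whether failing it makes a person ineligible.
- Refuses after randomisation: enrolled, and counted as a dropout.

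**2. The rate as written and the rate with refusals counted**

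Let E be the number enrolled, O those eligible but not enrolled for other reasons, and R those who decline at screening.

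- Rate as written: E/(E+O). R does not appear.
- Rate with refusals counted: E/(E+O+R).

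The first is never below the second, and is above it whenever R > 0.

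Inputs: E = 460 from the Sample size section ("The target sample size across all sites is 460"). O and R are not in the article; the values below are assumptions chosen to show a range.

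With O = 0, the rate as written is 460/460 = 100% for any R. Counting refusals:
- R = 115: 460/575 = 80.0%
- R = 230: 460/690 = 66.7%
- R = 460: 460/920 = 50.0%

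With O = 115, the rate as written is 460/575 = 80.0% for any R. Counting refusals:
- R = 115: 460/690 = 66.7%
- R = 230: 460/805 = 57.1%
- R = 460: 460/1035 = 44.4%

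Across these cases the overstatement runs from 80.0 − 66.7 = 13.3 to 100 − 50.0 = 50.0 percentage points. The spread reflects the assumed counts and is not an estimate for this trial.

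**3. Effect on the overall screening yield**

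With S people screened, E/S = [(E+O)/S] × [E/(E+O)]. Moving R people from eligible to ineligible multiplies the second factor by (E+O+R)/(E+O) and divides the first by the same amount. With O = 115 and R = 230 that factor is 805/575 = 1.4. The product E/S does not change.

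**The case against.** Several points on the other side have force.

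- *Willingness criteria are routine.* True, and the criterion itself is not at fault. The problem is its pairing with a primary outcome whose denominator is eligible people.
- *An article may leave the handling of refusals to the full protocol, and the eligibility-screening and participant-flow figures are not shown.* A site may well log decliners as eligible. But the article does not leave the denominator open: it states both what eligibility contains and that the rate is taken over eligible people. The objection is to those two statements together, not to missing detail.
- *Rejection of the system shows up elsewhere.* In part: dropout, adherence, usability scores and exit interviews all capture reactions after enrolment, but none captures refusal at the call. It is also true that recruitment precedes allocation, so it describes the trial as a whole and cannot isolate rejection of the technology arms under any denominator.

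A reader might also infer stronger claims that the documents do not support.

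- *The measure is fully circular and must come out at 100%.* It is not. Non-attenders and non-consenters after the call remain in the denominator, and 100% requires O = 0.
- *Unwillingness to accept allocation is likewise an eligibility failure.* That requirement is outside Table 1, and its effect on the denominator is unclear. Nor does Table 1 name the headset or sensors; refusing them fails the criterion only in so far as they belong to the proposed training.
- *The definitive trial would plan to screen too few people.* This does not follow. Enrolled over screened is unaffected, and the article commits to recording participant flow in line with CONSORT.

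**Conclusion.** The point holds in a limited form. Read as written, the primary recruitment rate excludes people who decline the training or testing at telephone screening, so it cannot respond to those refusals and overstates uptake among otherwise suitable people. The direction follows from the article's own definitions and needs no assumption about numbers beyond there being at least one such refusal. The size cannot be computed, because no refusal count is given. The conclusion rests on sites applying the willingness criterion literally at the call. It concerns the meaning of a primary acceptability measure. Randomised comparisons and the overall screening yield are not affected. It is worth correcting because the definition is stated, the measure is primary, and the change is small.

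**What to change.** In Primary outcome measures, define the recruitment denominator as people not ruled out on the clinical inclusion and exclusion criteria that can be assessed at the point of contact, disregarding the willingness and consent items. Count those who decline the equipment, the regime or the allocation as eligible but not enrolled, and record the reason (technology, exercise burden, allocation, other). Report enrolled over screened beside it. State this once so that all five sites classify decliners alike. The entry criteria do not change.

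The cost is one revised definition and a reason-for-decline field on the screening log. The reported percentage will be lower wherever there are such refusals. There is also a limitation to state: a person who declines by telephone may never complete measures such as the FGA, which consists of walking tasks, or the MoCA. Some decliners counted as eligible might therefore have failed a criterion measured later, and the revised rate may then somewhat understate uptake. That is why the denominator should be people not ruled out at contact; meeting every Table 1 criterion often could not be established for them.
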